### Eligibility criteria

#### Inclusion criteria

Aged 10–19 years old (33).According to “Chinese guidelines for diagnosis and treatment of polycystic ovary syndrome,” which was developed by the Endocrinology Group of the Chinese Medical Association Obstetrics and Gynecology Branch in 2018 (34), PCOS participants in the study must meet all three indicators in the Rotterdam diagnostic criteria at the same time (35), including: (i) oligomenorrhea persisting for at least 2 years after menarche, or amenorrhea; (ii) clinical manifestations of hyperandrogenism or hyperandrogenemia; (iii) the diagnosis of PCO on ultra sound includes increased ovarian size (>10 cm^3^).Able to self-report (verbally understandable and articulate).Participants and their families volunteer to participate in the study.

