#### Dependent variables

Depression will be measured by the Chinese version of the Children's Depression Scale(CDI) (38). The scale is comprised of 27 items, each of which offers three possible replies based on the respondent's actual mood during the previous 2 weeks. The project consists of five dimensions: anhedonia, poor efficacy, low self-esteem, negative emotions, and interpersonal problems. The intensity of each item determined whether it was rated zero, one, or two, and the negative word statement was scored in reverse. A score of 19 indicated the presence of depressive symptoms. It has been reported that the Chinese version of the CDI scale has been applied to children and adolescents ranging from 7 to 18 years of age in China (38–40). CDI has the advantage of having the lowest reading level of all depression measurement tools (only the first grade level). The Chinese version of the CDI scale has a good level of reliability and validity, as well as a high clinical diagnostic value for depression, and can be used to measure depression in children and adolescents in China. Utilize the total score to reflect the severity of depressive symptoms or diagnostic threshold due to its operability and clinical applicability.

We will use the Kiddie-Schedule for Affective Disorders and Schizophrenia-Epidemiological version (K-SADS-E) to confirm the diagnosis of depression and exclude possible comorbidities. The validated Mandarin version will be used in this study (41). It is a semi-structured diagnostic interview questionnaire designed to assess the current and past mental health status of children and adolescents aged 6-18 in accordance with the diagnostic criteria of the Diagnostic and Statistical Manual of Mental Disorders, 5th edition (DSM-5). In this study, two psychiatrists trained in K-SADS-E interview harmonization will conduct interviews to diagnose depression and exclude possible comorbidities. It will take approximately 1–1.5 h for each participant and their parents to complete the interview. It has been demonstrated that K-SADS-E has good psychometric properties (41). The diagnoses of K-SADS-E demonstrated good convergent and divergent validity with most corresponding clinical questionnaires.

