### Data collection

Two uniformly trained researchers will identified participants based on inclusion and exclusion criteria. Firstly, a researcher will guide participants and their parents to a quiet outpatient room that is conducive to dialogue and data collection. Another researcher will explain the purpose, significance, and implementation of the study to participants and their parents in a one-on-one format, assuring them that their privacy would be protected. With the consent of participants and their parents, researchers will sign informed consent forms with them. Afterwards, psychiatrists within the study team will conduct semi-structured interviews with participants and their parents, focusing on the diagnosis of depression and excluding possible comorbidities. The researchers will distribute the QR code of the scale that was included in the questionnaire platform in advance to participants who are eligible, and the participants will scan the QR code on WeChat to fill out the form online. Finally, the researchers will give the participants health education and prescription advice, as well as recording laboratory indicators including sex hormones and insulin. The total planned time for this process will be around 2 h. The data will be extracted *via* a questionnaire platform and collated into Excel format, with the two researchers collecting the information independently and negotiating any disagreements.

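### The outcome the model predicts is not fixed: the plan gives a CDI score, a CDI cut-off of 19 and a K-SADS-E diagnosis, and its analysis text mixes binary and continuous methods

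*Protocol article*

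**What the plan says.** All references are to the protocol article.

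- *Dependent variables* opens by assigning the measurement of depression to the CDI (27 items scored 0, 1 or 2). It gives a cut-off: "A score of 19 indicated the presence of depressive symptoms". It then says: "Utilize the total score to reflect the severity of depressive symptoms or diagnostic threshold due to its operability and clinical applicability".
- The same section adds the K-SADS-E, a psychiatrist-led interview against DSM-5 criteria, "to confirm the diagnosis of depression and exclude possible comorbidities". It budgets 1 to 1.5 hours for each participant and her parents.
- *Data collection* gives the order. After consent, "Afterwards, psychiatrists within the study team will conduct semi-structured interviews with participants and their parents, focusing on the diagnosis of depression". The online scales follow. The interview is not restricted to participants with a high CDI score.
- *Sample size and calculation* works with a binary outcome and an anticipated proportion of 0.4, tied to neither instrument.
- *Internal validation and assessment of model performance* chooses lambda by a one-standard-error rule on mean square error and then builds a multivariate linear model. It assesses performance by the C-statistic and by calibration of absolute risk.
- The *Introduction* describes the high-risk group as people with some depressive symptoms who fall short of the diagnostic criteria.
- On age, *Inclusion criteria* has "Aged 10–19 years old". The CDI is described as "applied to children and adolescents ranging from 7 to 18 years of age in China", and the K-SADS-E as designed for "children and adolescents aged 6-18".

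**The concern.** A prediction model is defined by the event it predicts. A score from 0 to 54, a symptom cut-off and an interview diagnosis are different outcome variables. They can give different coefficients, a different calibration and a different nomogram. *Dependent variables* is the place to choose among them, but it joins alternatives with an *or* and adds a further measure without a rule for combining them. This is therefore a conflict in the text that defines the outcome, and not a detail that an analysis plan could be expected to supply.

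The choice bears on the headline result. Many candidate predictors in Table 1 are questionnaire scales (sleep, interpersonal sensitivity, emotion regulation, body image, illness perception), collected in the same visit as the outcome. The CDI has its own dimensions for interpersonal problems and low self-esteem. A CDI outcome thus shares method and content with the predictors, which can raise apparent discrimination. An interview diagnosis by psychiatrists, with parents present, is less exposed. If the outcome is not fixed before analysis, nothing in the plan prevents the choice from being made with the results in view.

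**Working it through.** **1. Which outcome type does each part of the plan imply?**

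| Section | Element | Outcome implied |
|---|---|---|
| Dependent variables | CDI total for severity | continuous, 0 to 27 × 2 = 54 |
| Dependent variables | CDI at 19 (≥ or > not written) | binary, symptoms |
| Dependent variables | K-SADS-E | binary, DSM-5 diagnosis |
| Sample size and calculation | proportion 0.4 | binary, instrument not named |
| Model-building procedures | outcome placed in Y vectors | not stated |
| Internal validation | mean square error, linear model | continuous |
| Internal validation | C-statistic, absolute-risk calibration | binary |

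The binary elements outnumber the continuous ones. None of them chooses between the CDI cut-off and the K-SADS-E diagnosis.

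**2. Does the word *confirm* settle it?** It could suggest a sequence: CDI first, interview for those who screen positive. *Data collection* has the reverse order, with the interview first and the online scales afterwards, and no restriction by score. A screen-then-confirm outcome is therefore not what the plan describes.

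**3. Does the sample size depend on the choice?** The plan's formula is n = (1.96/δ)² × φ(1 − φ).

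The plan's own figure, with φ = 0.4 and δ = 0.05: (1.96/0.05)² × 0.4 × 0.6 = 1536.64 × 0.24 = 368.79, rounded up to 369. This reproduces.

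Other proportions with the same δ:

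| φ | n |
|---|---|
| 0.10 | 139 |
| 0.20 | 246 |
| 0.30 | 323 |
| 0.40 | 369 |
| 0.50 | 385 |
| 0.60 | 369 |

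Only 0.4 (*Sample size and calculation*) and 50–60% (*Introduction*) come from the document; 0.10 to 0.30 are assumed for the range. The product φ(1 − φ) peaks at φ = 0.5, where 1536.64 × 0.25 = 384.16, so n never exceeds 385. The plan expects 800 participants with PCOS. If they accrue evenly over the year (an assumption), January to August gives 800 × 8/12 ≈ 533 and the 80% training part gives about 427, still above 385. For a continuous CDI total the formula does not apply.

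**4. Age.** Inclusion covers ten single years of age (10 to 19). The stated ranges end at 18 for both the CDI and the K-SADS-E, so one year lies outside both. The document gives no age distribution, so the number of participants affected cannot be computed.

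**The case against.** The strongest reply is that the plan leans clearly towards a binary outcome. The sample size, C-statistic, absolute-risk language and nomogram all point that way, and the sentence on the total score can be read as describing two uses of one scale. The linear-model and mean-square-error wording could then be a slip in model specification. The K-SADS-E also stands under the dependent-variables heading, with psychiatrists making the diagnosis, so a reader may take the CDI as the symptom measure and the interview as the diagnosis.

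Much of this stands. The live question is mainly between two binary candidates, and it would overstate the case to call all three forms equally open. But the reply leaves those two unresolved, gives no rule for disagreement, and does not remove the continuous-outcome methods from the text.

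A reader might go further on several points that the document does not support:

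- *That 0.4 cannot be right for both the cut-off and the diagnosis.* It can: the two proportions are equal whenever false positives and false negatives are equal in number, even if individuals are classified differently.
- *That past episodes would count as events.* The mention of current and past status describes what the instrument covers; it is not an outcome rule.
- *That interviewers would know the CDI result.* The interview precedes the online scales, so study CDI scores should not yet exist.
- *That the age mismatch makes the outcome undefined.* It is a separate question of measurement validity. The CDI range is worded as reported use; only the K-SADS-E range is worded as a design range.

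**Conclusion.** The point holds as a conflict over the model's target. The plan does not say which variable is modelled or how CDI and K-SADS-E results are reconciled, and its analysis methods fit two different outcome types. This should be settled before any model is fitted.

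It is not a sample-size problem: on the plan's own criterion, 385 is the ceiling and 800 are planned. That criterion covers only the precision of the overall proportion.

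The inflation of discrimination under a CDI outcome is a reasoned expectation from shared method and content. The document offers no figure for it, and it would not arise in the same way if the interview diagnosis were the outcome. The age point is real but minor, and its size is unknown.

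**What to change.** 1. Name one binary outcome in *Dependent variables* before analysis. The preferred choice is current DSM-5 depressive disorder on the K-SADS-E: it is already planned for each participant, comes before the online scales, and shares less method and content with the self-report predictors. The word *current* also closes the question of past episodes.
2. Make the CDI at 19 (with ≥ or > stated) and the CDI total secondary outcomes, and say how disagreement between CDI and interview will be reported.
3. Align the rest with that outcome: a binary model family such as logistic LASSO in place of the linear model, a lambda criterion suited to it (for example binomial deviance), and a stated basis for the anticipated proportion.
4. Reconcile the outcome with the *Introduction*. A model for diagnosed disorder does not directly identify people who are symptomatic but below diagnostic criteria, so the authors should say what high risk will mean for the finished tool. If they prefer a CDI outcome for that reason, they should still name it alone and carry out step 3 for it.
5. Add a prespecified sensitivity analysis excluding 19-year-olds.

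The cost is mainly rewording, since the interviews are already in the schedule. The real downside is that prevalence under an interview diagnosis may differ from 0.4. This does not threaten the plan's precision target, but it changes the number of events: 800 × 0.4 = 320, against 800 × 0.2 = 160 at an assumed 0.2. Step 5 needs no new data.

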#### Independent variables

The predictors for building the model are shown in Table 1.

**Table 1 T1:** Model-building predictors: definition/measuring tools, variable type and units/categories.

**Candidate predictor**	**Definition/Measuring tools**	**Variable type**	**Units/categories**
**Individual susceptibility factors**			
Age	Adolescent's age	Continuous & Categorical	Years (age classified into approximately three to four categories)
Nationality	Adolescent's nationality	Binary	0 “the Han nationality” 1 “minority nationality”
Body mass index(BMI)	Body mass divided by the square of the body height	Continuous	kg/m^2^
Waist-to-hip ratio (WHR)	WHR is found by dividing circumference of the waist by the circumference of the hips	Continuous	
Living residence	Current residence of adolescents	Binary	0 “City” 1 “Countryside”
Education level	Current educational level of adolescents	Categorical	Education level classified into approximately five categories
Single parent family	Adolescents live with only one parent	Binary	0 “No” 1 “Yes”
Family history of mental illness	Mental illness within three generations in the paternal, maternal, direct and collateral lines in adolescents	Binary	0 “No” 1 “Yes”
Duration of illness	Time since first diagnosis of PCOS	Categorical	Duration of illness classified into approximately five to six categories
Personality	Eysenck Personality Questionnaire-Junior (42)	Continuous	
Emotional regulation skills	Emotion Regulation Scale (43)	Continuous	
**Diagnosis and treatment factors**			
Medication use	Adolescents with PCOS taking some medications, such as metformin, oral contraceptives and so on. If yes, please specify the medicine	Binary & Categorical	0 “No” 1 “Yes” (medications classified into approximately four to five categories)
Duration of medicine use	Duration of medicine use since first diagnosis of PCOS	Categorical	Duration of medicine use classified into approximately five to six categories
**Biological factors**			
Sleep	Athens Insomnia Scale (44)	Continuous	
**Psychosocial environmental factors**			
Interpersonal sensitivity	Symptom Checklist-90 (45)	Continuous	
Social support	Medical Outcomes Study Social Support Survey (46)	Continuous	
**Clinical symptoms**			
Hirsutism	Ferriman-Gallwey Rating Scale (47)	Continuous	
Acne	Rosenfield Scale (48)	Continuous	
Body image	The Nagetive Physical Self Scale (49)	Continuous	
**Illness perception factors**			
Illness perception	The Brief Illness Perception Questionnaire (50)	Continuous	
**Laboratory investigations**			
Sex hormone-binding globulin	Electro chemiluminescent immunoassay(ECLIA)	Continuous	nmol/L
Free testosterone index		Continuous	
Estradiol		Continuous	pmol/L
Follicle stimulating hormone		Continuous	mIU/mL
Luteinizing hormone		Continuous	mIU/mL
Progesterone		Continuous	nmol/L
Prolactin		Continuous	mIU/L
Total testosterone		Continuous	nmol/L
Dehydroepiandrosterone sulphate		Continuous	μmol/L
Third-generation thyrotropin		Continuous	μIU/mL
Insulin		Continuous	μIU/mL

### Data collection

Two uniformly trained researchers will identified participants based on inclusion and exclusion criteria. Firstly, a researcher will guide participants and their parents to a quiet outpatient room that is conducive to dialogue and data collection. Another researcher will explain the purpose, significance, and implementation of the study to participants and their parents in a one-on-one format, assuring them that their privacy would be protected. With the consent of participants and their parents, researchers will sign informed consent forms with them. Afterwards, psychiatrists within the study team will conduct semi-structured interviews with participants and their parents, focusing on the diagnosis of depression and excluding possible comorbidities. The researchers will distribute the QR code of the scale that was included in the questionnaire platform in advance to participants who are eligible, and the participants will scan the QR code on WeChat to fill out the form online. Finally, the researchers will give the participants health education and prescription advice, as well as recording laboratory indicators including sex hormones and insulin. The total planned time for this process will be around 2 h. The data will be extracted *via* a questionnaire platform and collated into Excel format, with the two researchers collecting the information independently and negotiating any disagreements.

### Quality control

The screening process will strictly adhere to the inclusion and exclusion criteria.Prior to conducting formal research, researchers will receive standardized training.Before the survey, researchers will explain the contents and precautions of the questionnaire to participants and their families. To ensure participants understand items, researchers will use uniform language to explain them, while avoiding leading words.The questionnaire must be completed without omissions to ensure completeness of content and efficient recall.Two researchers check and correct any discrepancies with the original data to ensure accuracy.

### Sample size and calculation

In the case of a binary outcome, an approximate 95% confidence interval for the total outcome proportion (ϕ) is

$$\begin{array}{l} \hat{\phi }\pm 1.96\sqrt{\frac{\hat{\phi }\left(1-\hat{\phi }\right)}{n}}, \end{array}$$

Therefore, the absolute margin of error (δ) is $1.96\sqrt{\frac{\hat{\phi }\left(1-\hat{\phi }\right)}{n}}$

For this reason, in order to get an accurate estimate of the overall outcome probability in the target population, based on the expected outcome proportion ($\hat{\phi }$) and the desired margin of error, the required sample size is calculated as: $n={\left(\frac{1.96}{\delta }\right)}^{2}\hat{\phi }\left(1-\hat{\phi }\right)$.

In general, we advise aiming for a margin of error of <0.05. Then assuming an anticipated outcome proportion in the study population of 0.4, then a minimum of 369 participants is needed to aim for an estimation error of no more than 0.05 around the actual value of 0.4 (51).

The study will include all adolescents with PCOS who attend the gynecology clinic of the Affiliated Hospital of Zunyi Medical University between January 2022 and December 2022, with an estimated sample size of 800. This study will recruit 400 healthy adolescent girls as the control group.

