## Introduction

Polycystic Ovary Syndrome (PCOS) is a female endocrine metabolic disease of unknown etiology, with a prevalence of 5.6 to 11.04% in adolescence (1) and 10.26% in the Chinese adolescent population (2). Symptoms of PCOS include abnormal menstruation, infertility, hyperandrogenismia, and polycystic ovarian changes (3). It has been controversial and challenging to diagnose PCOS during adolescence due to the overlap between regular pubertal physiological changes (irregular menstrual cycles, acne, and polycystic ovarian morphology on pelvic ultrasound) and adult PCOS diagnostic criteria. Consensus statements on adult and pediatric health have acknowledged these challenges (4–6). To be more specific, challenges include the risk of under-diagnosis, delayed and/or poor diagnosis experiences (7), and over-diagnosis, as well as the additional risk of the use of inconsistent non-evidence-based approaches to PCOS diagnosis and management (8). PCOS generally begins after the first menarche in adolescence and lasts through the reproductive years and perimenopause. Besides affecting reproductive health, PCOS increases the risk of diseases such as type 2 diabetes, cardiovascular disease and endometrial cancer (9), as well as the development of psychiatric disorders. Adolescent girls with PCOS are 2.4 times more likely to suffer from depression than normal girls of the same age, about 50–60% (10, 11). A depressive disorder can result in great psychological and physical distress in adolescents, leading to suicide in over half of them, and it can affect the health and psychosocial functioning of adults as well (12). Studies have shown that PCOS can also lead to infertility in the long run (13). Nevertheless, recent studies suggest that PCOS on its own is not necessarily a cause of infertility (14). It is possible that infertility can be exacerbated by emotional and psychiatric problems in PCOS patients due to illness and fear of future infertility (14). Thus, it is recommended that psychological, emotional, and other non-medical measures be optimized in order to treat infertility, as well as increasing the attention given to depression in individuals with PCOS. PCOS, however, has no identified etiology and no specific treatment. Life management is recommended by international evidence-based guidelines as the ideal treatment for PCOS (15), but patients with the disorder have poor life management skills (16). The guideline declares that patients with PCOS can participate in better life management by improving their psychological status (4). There is no doubt that depression is a significant health issue that must be addressed in the management of adolescents with PCOS.

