
**Figure 1 F1:**
[figure not shown]
Simulation map of risk factors for depression in adolescents with PCOS.

As previously noted, the occurrence of depression in adolescents with PCOS involves multiple dimensions and contains numerous independent variables. To minimize the bias caused by the absence of important independent variables, it's important to select as many variables as possible at the beginning of the warning model construction process. Traditional regression analysis methods using statistical software such as SPSS, Jamovi, etc., can quantitatively analyze the strength of a predictor based on the regression coefficient. However, conventional regression analysis methods cannot handle collinearity problems and produce high variance when there are numerous independent variables. Least Absolute Shrinkage and Selection Operator (LASSO) is a type of machine learning method introduced by Tibshiran in 1996 (26). On the one hand, LASSO can select features automatically. When there are numerous independent variables, LASSO can selectively integrate powerful explanatory factors into the model. On the other hand, LASSO can compress the coefficients of some minor or insignificant independent variables to zero and pick more relevant independent variables to prevent overfitting. As compared to traditional regression analysis methods, LASSO can process all independent variables simultaneously, which greatly increases the model's stability. LASSO has been gradually applied to the development of warning models in the medical area in recent years (27, 28), as it offers high stability, fast calculation speed, and ease of interpretation in building warning models. To date, LASSO has been applied to the construction of diagnostic prediction models, early risk identification of ischemic stroke, for example (27). LASSO has also been applied to the construction of prognostic prediction models, for instance, survival after ampullary adenocarcinoma resection (28). Additionally, a study based on LASSO used electronic primary care data to develop a predictive model of common mental disorders among adolescents and early adults (29). But the study noted that primary care data underestimated common mental disorders. Due to race and PCOS, the model cannot predict depression with PCOS in adolescents. Thus, we will explore the causes of depression in teenagers with PCOS and the influence of a variety of risk variables, as well as develop and test a depression risk prediction model for adolescents with PCOS. Not only will this model be able to identify high-risk groups for depression with PCOS in adolescence, but also for high-risk groups of depression in general adolescent girls.

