#### Model-building procedures (including predictor selection)

After the data set is imported into the R software, it will be divided into 80% training data and 20% validation data. The training data will be used to build the warning model, and the validation data will be used for internal validation.

To begin with, we will use R software to read the features of the dataset. After that, we will load the two R packages “corrplot” and “glmnet.” By using the cor() function, we will create a correlation object “corrlate” and visualize the correlation coefficient. The predictors and outcome variables in the training and validation sets will be encoded into matrices, the predictors will be stored in X vectors, and the outcome variables in Y vectors. A LASSO regression will be performed when alpha is set to one. The program will then be run. When the parameter lambda is greater, the estimated parameters will also be compressed to a smaller degree. As lambda reaches a certain value, some variables that are not important to the model will be compressed to zero, indicating that these variables will be eliminated. Thus, the lambda corresponding to the optimal result, the influencing factors of preliminary screening, and the regression coefficient will be obtained.

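### The minimum of 369 secures only the precision of an overall proportion; it is no basis for developing a model with about 33–50 candidate parameters

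*Protocol article*

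**What the plan says.** Under Sample size and calculation, the protocol article starts from "an approximate 95% confidence interval for the total outcome proportion", sets the target with "we advise aiming for a margin of error of <0.05", and continues by "assuming an anticipated outcome proportion in the study population of 0.4". From this it concludes that "a minimum of 369 participants is needed to aim for an estimation error of no more than 0.05". The section then gives an expected 800 patients with PCOS and 400 healthy controls. It contains no criterion based on the number of predictors, events, shrinkage, discrimination or calibration.

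Objectives states the aim: to develop a depression prediction model and to validate it. The Introduction, in the text after Figure 1, wants to "select as many variables as possible at the beginning of the warning model construction process", and Table 1 lists 31 candidates. Patient recruitment assigns January–August 2022 to model construction and September–December 2022 to external validation. Of the construction data, "it will be divided into 80% training data and 20% validation data" (Model-building procedures).

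**The concern.** The stated minimum belongs to a different question from the study's own. A prevalence can be estimated to ±0.05 with 369 patients whether the model has 3 candidate parameters or 50. The reliability of a fitted model depends on how many parameters are screened against how many events, and on how strongly the predictors separate cases from non-cases.

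A reader who sees 369 called a minimum, and 800 expected, will take it that the model is comfortably sized. If it is not, variable selection will be unstable and the predicted risks too extreme. Those risks are what the nomogram is meant to deliver.

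**Working it through.** **1. The plan's own figure.** n = (1.96/δ)² × φ(1−φ). With δ = 0.05 and φ = 0.4: 1536.64 × 0.24 = 368.8, so 369. It reproduces. Nothing else enters the formula.

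**2. Patients available for fitting (derived; the article does not state them).**
- Even accrual of 800, controls not in the model: 800 × 8/12 = 533 for development; × 0.8 = 427 for training; about 107 held out.
- Clinic flow of 80–100 a month (Participants): 80 × 8 × 0.8 = 512 to 100 × 8 × 0.8 = 640.
- Controls included in the model: 1,200 × 8/12 × 0.8 = 640.

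**3. Candidate parameters (derived from Table 1, one parameter per scale score).** Twenty-six rows are single terms; five have several categories.
- Dummy coding: 26 + age 1–4 + education 4 + illness duration 4–5 + medication 4–6 + duration of medicine use 4–5 = 43–50.
- Rank coding of ordered variables, which Handling of predictors allows: 26 + 1 + 1 + 1 + 3 + 1 = about 33 (medication, being unordered, takes 3).

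The same section lets non-linear continuous predictors be cut into categories, so the count can also rise.

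**4. Events per candidate parameter at 0.4.**

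| Training n | Events | 33 parameters | 43 | 50 |
|---|---|---|---|---|
| 427 | 171 | 5.2 | 4.0 | 3.4 |
| 512 | 205 | 6.2 | 4.8 | 4.1 |
| 640 | 256 | 7.8 | 6.0 | 5.1 |

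At 0.5 with 427 patients there are about 213 events: 6.5, 5.0 and 4.3.

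**5. Expected shrinkage (unpenalised benchmark).** n = k/[(S−1) ln(1−R²/S)], where k is the number of parameters, S the expected shrinkage factor and R² the Cox–Snell value. The article gives no expected performance, so C is an assumption. With normally distributed scores of equal variance in cases and non-cases, and prevalence 0.4, C = 0.75, 0.80 and 0.85 correspond to R² of about 0.179, 0.253 and 0.337.

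Example: 50 parameters, C = 0.75, S = 0.642: 50/[0.358 × 0.327] ≈ 427. So with 427 patients expected shrinkage is 0.64.

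| Patients | Parameters | C 0.75 | C 0.80 | C 0.85 |
|---|---|---|---|---|
| 427 | 50 | 0.64 | 0.73 | 0.79 |
| 427 | 43 | 0.67 | 0.75 | 0.81 |
| 427 | 33 | 0.73 | 0.80 | 0.85 |
| 640 | 43 | 0.75 | 0.82 | 0.86 |
| 640 | 33 | 0.80 | 0.85 | 0.89 |

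For S = 0.9, 33 parameters need about 1,490, 1,000 and 700 patients at C = 0.75, 0.80 and 0.85; 43 parameters need about 1,940 and 1,300 at the first two.

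**6. The 0.4 against the Introduction.** The Introduction says that girls with PCOS are "2.4 times more likely to suffer from depression than normal girls of the same age, about 50–60" per cent. The same formula gives 385 at 0.5, 381 at 0.55 and 369 again at 0.6, because φ(1−φ) is equal at 0.4 and 0.6.

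**The case against.** **LASSO is planned, and the benchmark is unpenalised.** This is fair as to exact size: the benchmark is an indication, not a forecast of the LASSO fit. But the section on internal validation uses LASSO to screen variables and then constructs a new model on those retained, without saying that the shrinkage is kept. Penalisation lessens overfitting; it does not turn 369 into a basis for model development.

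**The inputs are derived and C is assumed.** This stands, and is why ranges are given. The kindest corners do escape: at C = 0.90, 33 parameters need about 503 patients, which clinic flow would meet. Across C of 0.75–0.85 no combination reaches 0.9.

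**The article condenses a fuller plan.** Missing detail would be no finding. The point here is a criterion that the article does state, and calls a minimum, but that does not serve its stated aim.

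Three stronger readings might be inferred, and the document does not support them:
- *The 0.4 conflicts with 50–60% and invalidates the figure.* The input is unexplained, but it moves n by at most 16, and 800 exceeds 385. If the study population includes the controls, the two agree: (800 × 0.5 + 400 × 0.5/2.4)/1,200 = 0.40. The article does not say whether it does.
- *The validation sets fail the ±0.05 standard.* At 0.4 the margins are ±0.093 with 107 and ±0.059 with 267, but the protocol applies its margin only to the overall proportion. Those sets exist to assess discrimination and calibration.
- *There are fewer than 4 events per parameter.* That holds only with 427 patients, dummy coding and a proportion of 0.4.

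**Conclusion.** The concern holds in this form: 369 is a correct prevalence-precision figure presented as the study's minimum, and the section offers nothing that bears on developing the model. On the document's own accrual, split and candidate list, most combinations give about 3.4–6 events per parameter. Expected shrinkage is about 0.64–0.85 with 427 patients and at most about 0.89 with 640 patients and 33 parameters. This rests on a proportion of 0.4, C between 0.75 and 0.85, and an unpenalised benchmark.

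A shortfall is likely; its size is uncertain. It does not show that the study is infeasible or that more patients must be enrolled. The unexplained 0.4 is a minor note.

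**What to change.** 1. **Develop on all January–August patients** (about 533) instead of 427. Replace the 20% hold-out with bootstrap or repeated cross-validation of the whole selection-and-fitting procedure, and keep September–December for temporal validation. The hold-out would contain only about 43 events (107 × 0.4).
2. **Fix a lean coding before outcomes are seen.** Keep age and the two durations continuous, use one coding each for age and medication, and drop either the free testosterone index or its components. This leaves 26 + 1 + 4 + 2 + 4 = 37, less 1–2, so about 35–36 parameters.
3. **Rewrite the sample-size section.** Describe 369 as a prevalence-precision figure only. State the candidate parameters, expected events and expected shrinkage as a limitation, and say which population the 0.4 refers to.

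**Cost.** One section is rewritten, Table 1 is trimmed, a few redundant candidates are lost, and the stated figures look less favourable. No enrolment is added. At C of 0.75–0.80, 36 parameters in 533 patients give shrinkage of about 0.75–0.82, against 0.64–0.75 for 43–50 parameters in 427. The deficit narrows but remains: at 0.9 the benchmark supports only about 12–18 parameters in 533 patients.
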